### Wait-list control group/standard treatment

Participants in the control condition will receive treatment as usual from a practitioner who has not been trained in the Let’s Talk model (Table 1).

### Outcome measures

The primary outcome measures included the *Parental Stress Scale* [13] that measures perceived parenting stress and includes 18 items that together measure total parenting stress along with four subscales of parental rewards, parental stressors, lack of control and parental satisfaction. The *General Functioning Index* of the *McMaster Family Assessment Device* [14] measures family functioning. The General Functioning Index consists of 12 items and measures an overall score of family functioning that distinguishes between ‘effective and problematic’ family functioning. The *SF-12v2 Health Survey* [15] will be used as a measure of quality of life. The survey is a 12 item quantitative instrument that records impacts of mental and physical health on daily activities. Outcomes were measured at 6 months followup.

The secondary outcome measures were the *Parenting Self-Agency Measure* [16] that assesses the general level of confidence parents have in their ability to engage in successful parenting behaviours. The measure examines the domains of confidence, helplessness in the face of child opposition, ability to resolve parent-child conflict, and effort in parenting and persistence. The *Recovery Assessment Scale* [17] is a 22-item recovery scale commonly used in mental health services. It includes five subscales as well as a total score: Personal confidence and hope; Willingness to ask for help; Goal and success orientation; Reliance on others; and No domination by symptoms. Each of the above measures has been widely used and are well validated and exhibit strong internal consistency.

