### Participant numbers

A total of 192 parents will be recruited. Participant numbers were initially determined by a power calculation indicating a minimum *n* = 54 participants with Crit F = 2.46 (using GPOWER 3.1, assuming 3 repetitions, a small effect size, an alpha of 5% and power of 95%) to be required. The larger number of participants will account for parent dropout and to allow between group comparisons across sectors (*n* = 32 per sector per group for both intervention and control groups).

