## Design and statistical analysis

### Quantitative data analysis

The impact of Let’s Talk on parent-clients will be examined pre, post and follow-up using analyses of variance on each of the measures outlined above. There will be a within-subjects factor (time) and a between subjects factor (intervention/control and sector of participants – adult, community and family sectors). It is intended that analyses will be undertaken on intention to treat data however deviations from protocol adherence will also be examined including any differences between participant groups on demographic characteristics.

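### Three unranked primary measures each get their own ANOVA, while the sample size rests on one test at an unadjusted 5%; no rule says which result decides the trial

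*Protocol article*

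**What the plan says.** All references are to the protocol article.

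- **Outcome measures.** Three measures are primary. The list opens with "The primary outcome measures included the" Parental Stress Scale, which yields "total parenting stress along with four subscales of parental rewards, parental stressors, lack of control and parental satisfaction". The second: "The General Functioning Index consists of 12 items and measures an overall score of family functioning". The third: "The *SF-12v2 Health Survey* [15] will be used as a measure of quality of life". None is put ahead of the others. The section places the outcomes at the 6-month follow-up.
- **Quantitative data analysis.** The effect is examined "using analyses of variance on each of the measures outlined above". On the factors: "There will be a within-subjects factor (time) and a between subjects factor (intervention/control and sector of participants".
- **Participant numbers.** The GPOWER calculation uses three repetitions, a small effect, and "an alpha of 5% and power of 95" per cent. It reports a minimum n of 54 and a critical F of 2.46. The recruitment target is 192.
- **Background.** Three hypotheses cover recovery, parenting competence and self-efficacy, and family functioning. Each carries its own threshold, printed as p < 0.5.

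**The concern.** Which measures are primary, and the alpha behind the sample size, are protocol content, and the article states both. They do not fit together: three primary tests are declared, but the trial is sized as though there were one. Nothing says whether one, some or all of the three must be significant for the trial to count as positive.

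The hypotheses do not fill the gap. Family functioning is the only one that clearly matches a primary measure. Parental stress, the first primary named, is in none of them. Recovery and parenting self-efficacy lead the hypotheses, yet the scales for them are listed as secondary.

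What is at stake is how the result is read. Without a rule fixed beforehand, the deciding measure can be picked after the data are seen, and one nominal success among three can be presented as a positive trial at more than the 5% error rate used in planning.

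**Working it through.** **1. Which alpha the plan used.** With three groups, three repetitions and N = 54, the group-by-time test has (3 − 1)(3 − 1) = 4 and (54 − 3)(3 − 1) = 102 degrees of freedom. The 5% critical value of F(4, 102) is 2.461, which matches the printed 2.46. So the calculation is for one test at an unadjusted 0.05. The n of 54 follows only with f = 0.25: with an assumed correlation of 0.5 between repeats, power is 95.8%. Taking small to mean f = 0.10 (assumed; the article gives no number), power at N = 54 is 25.1%. That mismatch is a separate matter, but the power must be restated in any case.

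**2. Chance of at least one false primary claim, if any one of three suffices.** Inputs: three tests (one per primary measure), 0.05 each, no true effect on any.

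- Independent tests: 1 − 0.95³ = 1 − 0.857 = 14.3%.
- Upper bound under any dependence: 3 × 0.05 = 15%.
- Correlated tests: with a common correlation r between two-sided normal test statistics, and for comparison with a 2-df arm-by-time test (simulated):

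| Assumed r | Two-sided z | 2-df test |
|---|---|---|
| 0 | 14.3% | 14.2% |
| 0.3 | 13.6% | 13.7% |
| 0.5 | 12.5% | 12.8% |
| 0.7 | 10.9% | 11.1% |
| 0.9 | 8.4% | not run |

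Three is the smallest count. Testing subscales, more than one SF-12v2 score, or several F tests from each ANOVA would raise the rate; four independent tests give 1 − 0.95⁴ = 18.5%.

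**3. If all three must be significant.** With no true effect on at least one measure, a false overall claim needs that measure's test to be wrong, so the rate is at most 5%. Power is what suffers. With 95% power for each, the chance that all three succeed is at least 1 − 3 × 0.05 = 85% and at most 95% (0.95³ = 85.7% if independent). Participant numbers gives no such joint figure.

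**4. The printed p < 0.5.** Taken literally, three independent tests would give 1 − 0.5³ = 87.5%. The critical F supports 5% as the working level. Correcting 0.5 to 0.05 leaves step 2 unchanged.

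**5. Cost of adjusting.** Holm's first step uses 0.05/3 = 0.0167. For a single two-sided comparison, power becomes Φ(z₀.₉₇₅ + z_power − z₀.₉₉₁₇):

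- from 95%: Φ(1.960 + 1.645 − 2.394) = Φ(1.211) = 89%;
- from 80%: Φ(1.960 + 0.842 − 2.394) = Φ(0.408) = 66%.

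At this trial's size (N = 192, two arms, 2-df arm-by-time test, assumed f = 0.10 and correlation 0.5 between repeats, no dropout or clustering), the noncentrality is 0.10² × 192 × 3 / (1 − 0.5) = 11.52. Power is 86.6% at 0.05 (critical F 3.02) and 75.1% at 0.0167 (critical F 4.14).

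**The case against.** The strongest reply is that a multiplicity rule is an ordinary item for a statistical analysis plan. None is shown here, and a condensed article need not carry it. That stands as far as it goes: an unseen plan may contain such a rule, and its absence alone would be no finding. It does not remove the mismatch between what the article does state, three primary measures and a sample size for one test. A later split of alpha would depart from the stated power basis; a later all-three requirement would need joint power that was not computed.

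The reply also limits how far the point can be taken. A reader might infer three stronger things that the article does not support:

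- **That the plan breaks a promised trial-wide 5%.** No family-wise rate is claimed. The 5% appears only as an input to the power calculation, and treating each hypothesis as its own claim is a defensible position.
- **That the rate should be counted over every hypothesised dimension.** The recovery scale and the parenting self-agency measure are secondary, and dimensions of one construct in the same people are unlikely to be independent. Such a count says nothing about primary claims.
- **That one false primary result would by itself carry the case for a wider roll-out.** The article ties that case to the economic evaluation, with cost per quality-adjusted life year and sensitivity analyses, and not to one primary p-value.

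**Conclusion.** The point holds in conditional form. The article fixes three unranked primary measures, an ANOVA on each, and one unadjusted 5% behind the sample size, and it leaves open which result decides the trial. If any one of the three is enough, the chance of a false primary claim is 14.3% under independence and about 11% at a correlation of 0.7; even at 0.9 it stays above 5%.

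Those figures assume no effect on any of the three, one test per measure, each ANOVA holding its own 5%, and correlations that the article does not give. They are not an estimate of this trial's actual error rate. Under an all-three rule there is no inflation, only a loss of power that has not been worked out. The matter should be settled before analysis; it does not invalidate the design.

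**What to change.** State the decision rule in one or two sentences, in either form:

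- name one of the three measures as the sole primary and make the other two secondary; or
- keep all three, fix one score for each (the Parental Stress Scale total, with its subscales secondary, and one named SF-12v2 score), test each at the 6-month follow-up, and apply Holm across the three at an overall 5%.

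If the intention is that all three must be significant, saying so also removes the inflation. In every case, restate the power on the chosen basis, and reconcile the p < 0.5 in the hypotheses with the 5% in Participant numbers.

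A sole primary costs no alpha, but the other two measures can then no longer decide the trial. Holm costs the power shown in step 5 at its strictest step; the later steps, at 0.025 and 0.05, cost less. An all-three rule costs the joint power shown in step 3.

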#### Economic evaluation

An economic evaluation will be conducted examining the costs of delivering the program (sourced from practitioner records) combined with costs for individuals of accessing treatment (using retrospective self-reported medication and hospital use along with patient and carer time away from usual duties). The evaluation takes a societal perspective including financial implications to the health system and individual patients and their carers. Outcomes will consist of the trial measures: impact on disease recovery rates and quality of life impacts (converting the SF-12 scores to SF-6D utility measures suitable for economic evaluation [18]. Incremental cost-effectiveness will involve the comparison between intervention and control groups of cost per additional person recovered and cost per quality adjusted life year gained using impacts from the SF-12. The cost-effectiveness model will take the form of a decision analysis modelling people between mentally ill and recovered health states, with results presented initially for 12 months follow up. Modelling to full life expectancy will be performed incorporating lifetime costs associated with mental illness sourced from the scientific literature. Extensive one-way and probabilistic sensitivity analyses will be conducted to assess the impact of uncertainty on results.

#### Fidelity adherence

Fidelity to the Let’s Talk method will be measured through multiple means. Firstly, trained practitioners will be required to attend monthly practice development sessions to report on their delivery of the intervention in practice. Secondly, practitioners will be required to complete a fidelity checklist recording each session, the duration and content of the session, as part of their standard record keeping. These checklists will be provided to the researchers at the completion of the intervention, and used as a measure of fidelity of the delivery of the intervention.

**Table 1 Tab1:**
[figure not shown]
Overview of the research protocol for numbers to be enrolled, the intervention delivered, and measurement tools utilized throughout the study

t_1_ refers to the baseline measure, t_2_ is the post intervention or equivalent measure, and t_3_ is the 6 month follow-up measure post intervention

### Participant numbers

A total of 192 parents will be recruited. Participant numbers were initially determined by a power calculation indicating a minimum *n* = 54 participants with Crit F = 2.46 (using GPOWER 3.1, assuming 3 repetitions, a small effect size, an alpha of 5% and power of 95%) to be required. The larger number of participants will account for parent dropout and to allow between group comparisons across sectors (*n* = 32 per sector per group for both intervention and control groups).

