## Methods

### Design

This two-arm parallel randomised controlled trial will compare outcomes at post-test and 6 month follow-up (Trial register number ACTRN12616000460404) for Let’s Talk and control participants from the adult mental health, community mental health and family services. The protocol is in accord with the CONSORT-EHEALTH checklist. The study commenced in 2013 and will be completed in 2017.

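### The printed critical F of 2.46 cannot come from a two-arm, three-wave comparison, so the stated minimum of 54 and 95% power do not describe Let's Talk versus control

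*Protocol article*

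**What the plan says.** The sample-size statement is in the protocol article, section Participant numbers. It gives "a minimum *n* = 54 participants with Crit F = 2.46", obtained "using GPOWER 3.1, assuming 3 repetitions, a small effect size", with "an alpha of 5% and power of 95"%. The section then sets recruitment at 192, that is 32 parents in each of the six sector-by-arm cells, to cover dropout and to permit comparisons across sectors. It does not name the F test, the number of groups, the numerical effect size or the correlation between repeated measures.

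The comparison to be made is described elsewhere. Under Design: "This two-arm parallel randomised controlled trial will compare outcomes at post-test and 6 month follow-up". Under Quantitative data analysis, the model is an analysis of variance: "There will be a within-subjects factor (time) and a between subjects factor (intervention/control and sector of participants" being the three service sectors. The waves are baseline, post-intervention and six-month follow-up.

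**The concern.** A critical F is fixed by alpha and the two degrees of freedom. The numerator degrees of freedom follow from the number of groups and waves, so a printed critical F shows which test was powered. Here the value does not fit two arms measured three times. This sentence is the only power justification in the article. If it was computed for another test, readers have no stated minimum, and no stated power, for Let's Talk against treatment as usual.

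**Working it through.** **Inputs from the protocol article.** Three repetitions, alpha 0.05, power 0.95, minimum N = 54, critical F = 2.46 and 192 recruited (Participant numbers); two arms (Design); arm and three-level sector as between-subjects factors (Quantitative data analysis).

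**Inputs assumed.** Correlation ρ = 0.5 and sphericity ε = 1; Cohen's f = 0.10 for small and 0.25 for medium.

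**Formulas.** For a within-between interaction with k groups and m waves: df1 = (k − 1)(m − 1), df2 = (N − k)(m − 1), and noncentrality λ = f²·N·m/(1 − ρ). Power is the probability that a noncentral F with these degrees of freedom and λ exceeds the 5% critical value.

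**1. Reproducing the printed pair.** Take k = 3, m = 3, N = 54.
- df1 = 2 × 2 = 4 and df2 = 51 × 2 = 102. The critical F is 2.461.
- With f = 0.25, λ = 0.0625 × 54 × 3/0.5 = 20.25 and power is 0.958.
- At N = 51, the previous multiple of three, power is 0.946.

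One run with three groups therefore returns both 54 and 2.46.

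**2. The two-arm tests at N = 54.**

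| Test | df | 5% critical F |
|---|---|---|
| Arm by time | 2, 104 | 3.08 |
| Arm by time, multivariate | 2, 51 | 3.18 |
| Arm main effect | 1, 52 | 4.03 |

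As df2 grows without limit, the critical F on 2 numerator df falls only to 2.996. No sample size, effect size, correlation or power target brings it to 2.46.

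**3. Other tests in the planned model at N = 54.** All six arm-by-sector cells over time have df 10, 96 and critical F 1.93. Arm by sector by time has df 4, 96 and critical F 2.466, which rounds to 2.47.

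**4. The two-arm calculation (k = 2, ρ = 0.5, 95% power).**
- f = 0.25: minimum N = 44, critical F 3.11, power 0.956. At N = 54 power is 0.984.
- f = 0.10: minimum N = 260, critical F 3.01, power 0.951. At N = 54 power is 0.34.
- f = 0.10 at N = 192: λ = 0.01 × 192 × 3/0.5 = 11.52, df 2, 380, critical F 3.02, power 0.866.
- Effect detectable with 95% power at N = 192: λ must be about 15.6, so f = √(15.6 × 0.5/(3 × 192)) = 0.116.

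**5. Sensitivity to the correlation** (f = 0.10, N = 192). With ρ = 0.3, λ = 5.76/0.7 = 8.23 and power is 0.73. With ρ = 0.7, λ = 5.76/0.3 = 19.2 and power is 0.98.

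**6. Could 54 go with a small effect?** Only with a very high correlation: about 0.90 for two arms or 0.92 for three groups. Neither is stated.

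**The case against.** **The three-group reading is not documented.** This stands. The article states neither the test nor the number of groups. Arm by sector by time comes close: 2.466 would print as 2.46 if truncated, and 54 is also its minimum in multiples of six at f = 0.25 (power 0.929 at 48, 0.957 at 54). It needs truncation and a numerator df entered by hand, so three groups is the simpler fit. That term also asks whether the effect differs by sector, not whether Let's Talk works.

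**A three-group test may have been intended.** The Recruitment section keeps parents who decline Let's Talk as a further comparison group, so the three groups could be intervention, control and decliners, or the three sectors. Either is possible. Neither is the two-arm comparison, and decliners are not a randomised group.

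**The discrepancy is conservative.** For the number of groups alone, this stands. With f = 0.25, three groups give 54 and two arms give 44, and 192 exceeds both. A reader might infer that the wrong group count leaves the trial too small; the figures do not support that. The shortfall against 95% arises from the word small, not from the group count.

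**A reader might also infer an inflated type I error**, since 2.46 is too low a threshold on 2 numerator df (its tail probability at df 2, 104 is 0.090). The article does not support this. The 2.46 is an output of the power program. The planned analyses of variance will use the degrees of freedom of the fitted model, and no section makes F > 2.46 a decision rule.

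**Conclusion.** The figure is wrong as written. That 2.46 is not the 5% critical value for arm by time with two arms and three waves is certain and needs no unstated input: the value is 3.08 at N = 54 and at least 3.00 at any N. It follows that the stated minimum and 95% power do not describe Let's Talk versus control.

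The source of the pair, three groups by three waves at f = 0.25 and ρ = 0.5, is a strong inference and not a documented fact. If it is right, the same sentence also calls a conventionally medium effect small.

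The size of the problem depends on which effect was meant. Under ρ = 0.5, sphericity, no dropout and no clustering by practitioner, 192 parents give power close to 1 at f = 0.25 but about 87% at f = 0.10, where 260 would be needed for 95%. For ρ from 0.3 to 0.7 the power at f = 0.10 runs from about 73% to 98%. The defect lies in the stated basis for the sample size; it does not show that the planned analysis is invalid.

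**What to change.** Re-run the calculation with two groups for the arm-by-time effect (2 numerator df). State the numerical effect size, the correlation between waves and the test. Replace 54 and 2.46 with the resulting minimum and critical F, and report the power that 192 parents give. The effect size has to be settled in the same edit, because the result changes from 44 to 260 between f = 0.25 and f = 0.10 at ρ = 0.5.

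If a small effect is what was meant, keep 192 and restate the claim: either about 87% power at f = 0.10, or 95% power for f of about 0.116, both at ρ = 0.5 before dropout and clustering. If a three-group figure is kept for another purpose, label it as such and name the groups.

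The cost is one run of the power software and a rewritten sentence or two. No additional parents are required, provided the power or the detectable effect is restated and 95% at f = 0.10 is no longer claimed without support.

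### The stated 95% power for a small effect does not match n = 54 with Crit F = 2.46, which fit a medium effect in a three-group by time test

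*Protocol article*

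**What the plan says.** Under Participant numbers, the article gives a power calculation with a "minimum *n* = 54 participants with Crit F = 2.46", described as "using GPOWER 3.1, assuming 3 repetitions, a small effect size, an alpha of 5% and power of 95" per cent. It then enlarges that figure: "A total of 192 parents will be recruited". The reason given is that "The larger number of participants will account for parent dropout and to allow between group comparisons across sectors", with "32 per sector per group for both intervention and control groups".

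The section gives no numerical effect size, number of groups, correlation among the repeated measures, or type of F test. Under Design the trial has two arms: "This two-arm parallel randomised controlled trial will compare outcomes at post-test and 6 month follow-up". Under Quantitative data analysis the model is a mixed analysis of variance: "There will be a within-subjects factor (time) and a between subjects factor (intervention/control and sector of participants", the sectors being adult, community and family services.

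**The concern.** Fifty-four participants is very few for 95% power against a small effect, even with three measurements per person. The article also prints the critical F. That value depends only on alpha and the degrees of freedom, so it shows which test was powered without any assumption about correlation. If that test or the effect size is not the one described, the stated sensitivity does not belong to this trial. A reader of a null result could then take small effects to have been excluded with 95% power. The increase from 54 to 192 does not remove the problem by itself, because it is justified by dropout and sector comparisons and not by the number a small effect requires.

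**Working it through.** **Inputs from the article:** N = 54, critical F = 2.46, m = 3 repetitions, alpha 0.05, power 0.95, two arms, three sectors, 192 recruited.

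**Assumptions not in the article:** small is f = 0.10 and medium is f = 0.25 (the usual conventions); correlation rho = 0.5 and sphericity (the software defaults). Rho is varied below.

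**Formulas** (group by time interaction, k groups): df1 = (k−1)(m−1); df2 = (N−k)(m−1); noncentrality λ = f²·N·m/(1−rho); power from the noncentral F distribution.

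**1. Which test has critical F = 2.46 at N = 54?**
- k = 3: df1 = 2×2 = 4, df2 = 51×2 = 102, critical F = 2.461. This matches.
- k = 2 (the arms): F(2,104), 3.08.
- k = 6 (arm by sector cells): F(10,96), 1.93.
- Across 2 to 9 groups and 2 to 9 repetitions, only three groups with three repetitions gives 2.46 for the interaction.
- With three repetitions, the test of time alone gives 3.08 to 3.10. The between-groups test matches for no number of groups from 2 to 9 (2.56 for five, 2.41 for six).

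**2. Which effect size gives N = 54 with k = 3 and rho = 0.5?**
- f = 0.25: λ = 0.0625×54×3/0.5 = 20.25, power 0.958. At N = 51, λ = 19.125 and power is 0.946. So 54 is the smallest multiple of three that reaches 95%, and the article's figure is reproduced exactly.
- f = 0.10: λ = 0.01×54×3/0.5 = 3.24, power 0.251. The figure is not reproduced.
- f = 0.10 with k = 2: the same λ, power 0.336.

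**3. Could a higher correlation rescue the small effect at N = 54?** With three groups, 95% power for f = 0.10 needs rho of about 0.92 (0.917). With two arms it needs about 0.90. The questionnaires span more than six months (Data collection section), and no such value is stated.

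**4. Power for f = 0.10 by correlation, before dropout and clustering**

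| rho | N = 54, three groups | N = 54, two arms | N = 192, two arms |
|---|---|---|---|
| 0.3 | 19% | 25% | 73% |
| 0.5 | 25% | 34% | 87% |
| 0.6 | 31% | 41% | 93% |
| 0.7 | 41% | 52% | 98% |

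At N = 192 the two-arm test reaches 95% at rho of about 0.63. At rho = 0.5 it needs N = 260.

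**5. Effect detectable with 192.** For two arms at rho = 0.5, 95% power needs λ of about 0.01×260×3/0.5 = 15.6. With 192, f = √(15.6×0.5/(192×3)) = 0.116.

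**6. Illustration of dropout.** The article gives no rate, so the rates here are assumed. Two arms, f = 0.10:

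| Dropout | N | rho 0.5 | rho 0.7 |
|---|---|---|---|
| 0% | 192 | 86.6% | 98.1% |
| 20% | 154 | 77.8% | 94.7% |
| 30% | 134 | 71.5% | 91.3% |

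Clustering lowers these further, since practitioners are randomised and may each refer several parents (Recruitment section). With an assumed design effect of 1.2 (λ divided by 1.2) at N = 154, power is 69.5% at rho 0.5 and 90.1% at rho 0.7.

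**The case against.** Four points on the other side deserve weight.

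- **The correlation is unknown.** A reader might infer that 192 is too few for 95% power against a small effect. The document does not support this as a flat statement: it is true for the two-arm test only below a correlation of about 0.63 before losses, and at 0.7 power is 98%. The mismatch at 54 is much more robust, since two-arm power there is still only 52% at 0.7.
- **Four numerator degrees of freedom are not foreign to the plan.** Sector has three levels, so sector by time over three occasions has 4. The Recruitment section also keeps parents who decline the intervention as a separate comparison group. This stands: the calculation may have been run for a term or grouping that the plan contains. The article does not say so, and neither is the intervention-versus-control question.
- **Sector comparisons.** A reader might infer that these cannot be delivered at the stated power. The article attaches its 95% to the calculation for 54 and states no power for sectors. Within one sector (64 parents, rho 0.5) the arm by time test has 39% power at f = 0.10 but 99% at f = 0.25, so the answer depends on the very label in dispute.
- **Dropout.** A reader might infer that no allowance is left because 32×3×2 = 192. But 192 exceeds the stated minimum by 138, the 32 per cell can be read as an enrolment count, and no retained cell size is promised. This is not a contradiction.

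**Conclusion.** The power statement is wrong as written. That the critical F belongs to a three-group by time test follows from the printed figures and needs no assumed correlation. That the effect entered was medium and not small rests on the conventional labels and the default correlation of 0.5. The exact agreement at 54 makes this by far the likeliest explanation, but it remains an inference about the sponsor's inputs. On those assumptions, the real power for a small effect at 54 is about a quarter to a third, against the 95% claimed. The 192 parents are not shown to be inadequate. What is unsupported is a claim of 95% power for a small effect, overall or by sector, until a calculation with stated inputs bears it out.

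**What to change.** In the Participant numbers section:

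1. State the numerical f, the number of groups, the correlation and the F test that produced 54 and 2.46.
2. Replace the small-effect label with the effect size actually entered, which appears to be medium (f = 0.25). The sponsor should confirm this from its own record and not print the back-calculated inputs as fact.
3. Recalculate for the planned two-arm by time comparison over the three occasions.
4. Report the effect detectable with 192 recruited over a stated range of correlation, dropout and practitioner-clustering design effect.
5. Claim no 95% power for a small effect, overall or within sectors, unless that recalculation supports it.

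The cost is wording and one short recalculation. Enrolment does not change. The stated sensitivity will probably look less favourable than it does now.

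### The stated 54 parents do not give 95% power for a small effect unless the correlation between waves, which is not stated, is about 0.90 or higher

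*Protocol article*

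**What the plan says.** The Participant numbers section describes "a power calculation indicating a minimum *n* = 54 participants with Crit F = 2.46". The inputs are listed as "using GPOWER 3.1, assuming 3 repetitions, a small effect size, an alpha of 5% and power of 95" per cent. No numeric effect size, between-wave correlation, number of groups or named F test is given.

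The section also states "A total of 192 parents will be recruited". It explains the larger number as cover for dropout and as room for comparisons between sectors, with 32 parents "per sector per group for both intervention and control groups". The cells add up: 32 × 3 sectors × 2 groups = 192.

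The Quantitative data analysis section plans analyses of variance with time as the within-subjects factor and with arm and sector between subjects. The Design section describes a two-arm parallel trial.

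**The concern.** Three repeated measures, a small effect, 5% alpha and 95% power would normally call for several hundred participants, so 54 looks too low. If the input was really a larger effect, the article claims more sensitivity than the calculation supports. The target of 192 is presented as a larger number than the minimum, so a wrong minimum also misstates how much room there is for dropout and sector comparisons. Anyone interpreting a null result will turn to this paragraph to see what size of effect the trial could have detected.

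**Working it through.** **Inputs from the article:** N = 54, critical F = 2.46, m = 3 repetitions, alpha 0.05, power 0.95, planned N = 192.

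**Assumptions, not in the article:** small means Cohen's f = 0.10 and medium means f = 0.25. The correlation between waves, ρ, is 0.5 in the base case and is varied below. Sphericity holds, parents are independent, and there is no dropout.

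**Formula** (repeated-measures ANOVA, within-between interaction, k groups):
- df1 = (k − 1)(m − 1)
- df2 = (N − k)(m − 1)
- noncentrality λ = f² × N × m / (1 − ρ)
- power = P(noncentral F with df1, df2 and λ exceeds the 5% critical value)

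**Step 1: which design gives a critical F of 2.46 at N = 54?** The critical value depends on N, k, m and alpha, and not on effect size.
- Interaction, k = 3: df 4 and 102, critical F 2.461. This matches.
- Interaction, k = 2: df 2 and 104, critical F 3.08.
- Interaction, k = 6: df 10 and 96, critical F 1.93.
- Time effect only: 3.08 to 3.10.
- Between-groups effect with 2, 3 or 6 groups: 4.03, 3.18 or 2.41.

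Of the tests tried (1 to 8 groups), only the three-group interaction fits.

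**Step 2: reproduce 54.** With k = 3, ρ = 0.5 and f = 0.25, λ = 0.0625 × 54 × 3 / 0.5 = 20.25 and power is 0.958. At the next lower balanced size, N = 51, power is 0.946. The minimum is therefore exactly 54, and both printed figures are matched by a conventional medium effect.

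**Step 3: the effect as stated.** With f = 0.10 and ρ = 0.5, λ at N = 54 is 0.01 × 54 × 3 / 0.5 = 3.24.
- Power is 0.251 with k = 3 and 0.336 with k = 2.
- The N needed for 95% power is 312 with k = 3 (power 0.950) and 260 with k = 2 (power 0.951).

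**Step 4: vary the correlation, f = 0.10.**

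| ρ | N for 95%, two arms | N for 95%, three groups | Power at 54, two arms | Power at 54, three groups |
|---|---|---|---|---|
| 0.3 | 362 | 438 | 25% | 19% |
| 0.5 | 260 | 312 | 34% | 25% |
| 0.6 | 208 | 252 | 41% | 31% |
| 0.7 | 156 | 189 | 52% | 41% |
| 0.8 | 106 | 129 | 71% | 59% |

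A minimum of 54 is reached only at ρ of about 0.90 (two arms) or 0.92 (three groups). A need of 192 or fewer is reached from ρ of about 0.63 (two arms) or 0.70 (three groups).

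**Step 5: what 192 gives for arm by time (k = 2).** With f = 0.10 and ρ = 0.5, λ = 0.01 × 192 × 3 / 0.5 = 11.52 and power is 0.866. It is 0.727 at ρ = 0.3 and 0.981 at ρ = 0.7. At ρ = 0.5, 95% power is reached for f of about 0.12 (f = 0.116 gives 0.949 and f = 0.117 gives 0.953).

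**The case against.** The strongest reply is that the article states neither f nor ρ as a number, and N = 54 fixes only a combination of the two. With three groups, 54 is also the exact minimum for f = 0.20 at ρ of about 0.67 to 0.685, for f = 0.15 at about 0.82, and for f = 0.10 at about 0.92. The critical F says nothing about f. This stands, so the medium effect is the likeliest explanation and not a proven one. It does not rescue the statement as printed. For f = 0.10, power at 54 stays between 19% and 71% for every correlation in the table, whichever number of groups is used.

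A second reply is that recruitment rests on the cell rule of 32 per sector per group and not on 54. That is also right, so the number to recruit does not change.

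A reader might go further and infer that a small effect definitely needs more parents than the 192 planned. The documents do not support that. It holds only below a correlation of about 0.63 (two arms) or 0.70 (three groups), and the article gives no correlation. Nor does the article say that 192 gives 95% power for a small effect, or that a null result will be taken to exclude one. Misreading a null result is a risk that the wording invites, and is not something the plan proposes.

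**Conclusion.** The pairing of a small effect with 54 parents and 95% power is wrong as written for any plausible correlation. On the convention f = 0.10, and at correlations from 0.3 to 0.8, the true requirement is about 2 to 8 times 54 (106 / 54 ≈ 2.0; 438 / 54 ≈ 8.1). Separately, the printed critical F belongs to a three-group run. It therefore does not describe the two-arm by time comparison, whose critical value at N = 54 would be 3.08.

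These results rest on the conventional meaning of small, on sphericity and on independent parents with complete data. Dropout and clustering by practitioner, who is the unit of randomisation in the Recruitment section, are in none of the figures, and both would lower the power. Whether 192 is enough for a small effect remains open until the correlation is stated.

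**What to change.** In the Participant numbers section:

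1. State the f, the between-wave correlation, the number of groups and the F test actually entered.
2. If the sponsor confirms that f = 0.25 was the input, replace small with medium (f = 0.25). If a small effect was meant, correct the 54 instead.
3. Restate what 192 gives for the arm by time test, with its assumptions. At correlation 0.5, with no dropout or clustering, this is about 87% power for f = 0.10 (73% to 98% over correlations of 0.3 to 0.7), or 95% power for f of about 0.12. Say that dropout and clustering by practitioner would lower these figures.

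The cost is one rewritten paragraph and a less favourable stated power. The recruitment target, design and analysis do not change.
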